## Discussion

Rotator cuff injury is a common issue and can lead to serious shoulder dysfunction, thereby increasing the social burden [29]. PRP could promote tendon healing, and the goal of physiotherapy is to improve shoulder pain and dysfunction. Both PRP injection and physiotherapy could be applied in patients with rotator cuff injury. There is no definitive conclusion as to whether the combination is effective. We first combined PRP with physiotherapy for patients with rotator cuff injury, and we hypothesis that PRP injection in addition to early physiotherapy has an advantage over PRP injection alone. A prospective non-randomized study involving 314 participants will be implemented.

In recent years, PRP has become more and more popular in treating various musculoskeletal diseases due to the remarkable healing augmentation without severe side effects [30]. Several studies reported that PRP as a conservative approach to treat rotator cuff injury. Rha et al. supposed that PRP is safe and effective for rotator cuff disease [31]. Ilhanli I et al. showed that PRP might be as effective as physical therapy [32], PRP in addition to sodium hyaluronate have better clinical outcomes than PRP or sodium hyaluronate alone [11]. However, a high-level trial suggested that PRP cannot enhance tendon healing and improve clinical scores [33]. Most of the studies did not mention rehabilitation program after PRP injection; up to exercises were added [21, 22]. We have to continue exploring the effectiveness of PRP injection due to the evidence is low. Physiotherapy seems as a routine approach for rotator cuff diseases. Whether early physiotherapy could enhance the effects of PRP is unknown. A recent study showed that exercise can increase the concentration of platelets in PRP products [34]. This could be a theoretical foundation for our research. Meanwhile, the rehabilitation protocol, including exercise type, time, and treatment length is various [29]. A standardized rehabilitation protocol after PRP injection is needed.

Some limitations should be listed. First, the current study design is a non-randomized study. The evidence level is relatively low. Considering the feasibility and the actual situation, we select non-randomized study with a large sample size to clarify the correlation between PRP and physiotherapy. In our study, the participants have the right to receive physiotherapy or not. Second, it is impossible to blind therapists. We need therapists to protect participants. Except for limitations, we also have some strengths. This is the first study to analyze the PRP injection combined with physiotherapy for patients with rotator cuff injury. The study design is relatively humanized, and the results are objective. In addition, statistics experts will participate in this study to make the results more reliable. Finally, we can easily establish a clinical database based on this study.

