**Methods:**

This is a single-center prospective non-randomized study implemented in July 2019 at the Affiliated Hospital of Southwest Medical University in Sichuan. Three hundred-forteen patients with rotator cuff injury aged over 18 years were recruited. Participants were assigned to the experiment group (PRP plus physiotherapy) or control group (PRP) by their desire. We used the Constant-Murley score to assess the shoulder function, the Visual Analogue Scale to evaluate shoulder pain, and the MOS Item Short-form Health Survey (SF-12) to measure the quality of life. MRI was applied to measure tear size, and the follow-up duration is 12 months.

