### Study setting and participants

This study is being performed in the Affiliated Hospital of Southwest Medical University in China, and all participants are recruited from inpatient and outpatient. All patients were screened rigorously according to inclusion and exclusion criteria. Physicians decide whether the patient is enrolled, and they will tell eligible participants the research protocol in detail. Every eligible participant will be asked to sign a written consent before taking part in this study. The participants voluntarily choose to receive rehabilitation programs after PRP injection, then PRP in addition to physiotherapy group and PRP group were formed. The trial protocol is shown in Fig. 1.

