### Outcome measures

#### Primary outcomes

The primary outcomes of our study are the Constant-Murley score (CMS) and visual analog scale (VAS). The shoulder function of the patients will be measured by adopting CMS. CMS is a self and examiner based tool, including pain, the activity of daily life, range of motion, and muscle strength [26]. The total score is 100 and divide into four levels, excellent (< 11), good (11–20), fair (21–30), and poor (> 30) [27]. The overall shoulder pain will be assessed through a VAS, with a score of 0 (no pain) to 10 (maximal pain).

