#### Secondary outcomes

Tear size change assessed by MRI, the quality of life evaluated by Medical Outcomes Study Short Form 12-Item (SF-12), and adverse events will be recorded as secondary outcomes. An independent radiologist will assess tear size through MRI before PRP injection and 12 months follow-up. The SF-12 is a 12-item questionnaire, focusing on physical functioning, social functioning, bodily pain, vitality, role physical, role emotional, general health, and mental health [28]. In addition, any adverse events caused by PRP injection and physiotherapy will be recorded via self-report. The outcome indicators will be assessed at five different times by a blinded physiotherapist (Table 1).

**Table 1 Tab1:** Schedules for follow-up assessments and data collection

Assessments	Baseline (Two days after PRP injection)	Finish manual therapy			
		1 month	3 months	6 months	12 months
CMS	√	√	√	√	√
VAS	√	√	√	√	√
SF-12	√				√
Adverse effects	√	√	√	√	√
Tear size	√				√

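### The article calls its results objective and names only therapists as unblinded, although participants choose and know their treatment and both primary outcomes rest wholly or partly on their own reports

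*Protocol article*

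**What the plan says.** The Discussion of the Protocol article lists strengths and limitations. Among the strengths it says: "The study design is relatively humanized, and the results are objective". Its limitations are the non-randomized design, with a relatively low level of evidence, and blinding of one party: "Second, it is impossible to blind therapists". It adds that participants are free to take physiotherapy or not. It does not say that participants are unblinded.

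Other sections describe the features that bear on that claim:

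- **Allocation** (Study setting and participants): "The participants voluntarily choose to receive rehabilitation programs after PRP injection". The abstract agrees: "Participants were assigned to the experiment group (PRP plus physiotherapy) or control group (PRP) by their desire".
- **Treatment contrast** (Physiotherapy protocol): only the experiment group receives manual therapy, supervised exercise and home exercise. No sham or matched contact is described for the control group.
- **Primary outcomes**: CMS and a 0 to 10 pain VAS. Of the first the article says: "CMS is a self and examiner based tool, including pain, the activity of daily life, range of motion, and muscle strength".
- **Assessment** (Secondary outcomes): "The outcome indicators will be assessed at five different times by a blinded physiotherapist". Tear size on MRI is a secondary outcome, read by an independent radiologist. Data management adds that statisticians are blinded.

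**The concern.** For a self-reported item the rater is the patient. A blinded physiotherapist who writes down a pain score still records the judgement of someone who picked the treatment and knows whether it was given. All of VAS is of this kind. So, on the natural reading of the article's description, are the pain and daily-activity parts of CMS. Range of motion and strength are the examiner's part.

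The article therefore claims a property that its primary outcomes have only in part, and its blinding limitation stops short of the people who supply much of the data. Because pain enters both primary outcomes, a shift in reported pain moves both, and agreement between VAS and CMS is not independent confirmation.

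At stake is the interpretation of a positive result. The planned two-group tests cannot separate a gain in motion and strength from a change in how patients report pain and daily activity. Disclosing the non-randomized design does not cover this. That disclosure concerns who is in each group, whereas expectation in reporting would remain even if the groups were perfectly balanced.

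**Working it through.** **Step 1. Who rates what, and who is blinded.**

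| Outcome | Rater | Rater blinded? |
|---|---|---|
| VAS pain (primary) | patient | no |
| CMS pain, daily activity (primary) | patient | no |
| CMS range of motion, strength (primary) | physiotherapist | yes |
| MRI tear size (secondary) | independent radiologist | masking to group not stated |

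One primary outcome is wholly self-reported and the other is mixed.

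**Step 2. Inputs for a size.** From Sample size calculation: CMS difference 8, SD 20, 131 per group, alpha 0.05. Two-sided testing is assumed, because sidedness is not stated. The article gives neither a size for expectation bias nor the share of CMS points that is self-reported. Both are assumptions here: 35 of 100 points (range 25 to 50), and a shift of 10% of the range of those items.

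The plan's own figure was checked first. With n = 2 × [SD × (z for alpha + z for power) / difference]²:

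- 80% power: 2 × [20 × (1.960 + 0.842)/8]² = 98.1, so 99 per group
- 90% power: 2 × [20 × (1.960 + 1.282)/8]² = 131.3

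The stated 131 thus matches about 90% power rather than the stated 80%. That is a separate matter. Below, 131 is used as the planned analysed number per group.

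**Step 3. Bias on total CMS.**

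- 0.10 × 25 = 2.5 points; 2.5/8 = 31% of the planned difference
- 0.10 × 35 = 3.5 points; 3.5/8 = 44%
- 0.10 × 50 = 5.0 points; 5.0/8 = 63%

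**Step 4. Chance that such a bias gives a significant result with no true effect.**

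SE = 20 × √(2/131) = 2.47. The smallest significant difference is 1.96 × 2.47 = 4.84 points. For a net between-group bias b, the chance of a significant result favouring physiotherapy is 1 − Φ(1.96 − b/2.47):

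| b (CMS points) | Chance |
|---|---|
| 0 | 2.5% |
| 1 | 6.0% |
| 2 | 12.5% |
| 2.5 | 17% |
| 3 | 22.8% |
| 3.5 | 29% |
| 4 | 36.6% |
| 5 | 52.5% |
| 8 | 89.9% |

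**Step 5. How large the shift must be.** The bias equals the 4.84-point threshold, where the chance is 50%, when the self-reported items shift by 4.84/25 = 19%, 4.84/35 = 14% or 4.84/50 = 10% of their range.

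**Step 6. VAS.** A 10% shift is 1 point. The article gives no VAS SD. With an assumed SD of 2 to 3 and 131 per group, a 1-point bias is significant 98% to 77% of the time, and a 0.5-point bias 53% to 27%.

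**The case against.** The best defence is that much is already disclosed or mitigated. The article admits the non-randomized design, the low level of evidence and the patients' choice. It blinds the assessing physiotherapist and the statisticians, and has MRI read independently. Those safeguards may be what the word objective was meant to convey. Unblinded participants are also unavoidable when physiotherapy is added by choice, and therapist contact is arguably part of the package under test.

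Most of this stands as description. None of it reaches the self-reported items, and MRI tear size is only secondary. The criticism is of the claim and the missing limitation, not of the decision to run an open study.

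Four stronger readings are tempting, and the document does not support them:

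- **That only the total CMS will be analysed.** The article gives a total and names four components, and its analysis section is silent on the form used. Component scores may be covered in a full protocol or SAP that is not shown.
- **That assessor blinding protects neither primary outcome.** It does protect the examiner-measured part of CMS, which is 50 to 75 of 100 points under the assumption used here.
- **That expectation alone would produce a positive CMS result.** At the central assumption the bias is 3.5 points, below the 4.84-point threshold, and it reaches significance only about 29% of the time. The VAS figures are higher but depend on an SD that the article does not give.
- **That the final report will present a reporting effect as objective benefit.** No such report is at hand.

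**Conclusion.** The point holds in limited form. The objectivity statement is not supported by the article's own description of its primary outcomes, and the blinding limitation is too narrow because it omits participants. Expectation could contribute to a difference on VAS and on the self-reported part of CMS. Its size is unknown.

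The illustration of 2.5 to 5.0 CMS points, significant in favour of physiotherapy about 17% to 53% of the time against 2.5% without bias, rests on an assumed self-reported share of 25 to 50 points, an assumed 10% shift and two-sided testing. It shows that the bias could matter at the planned precision. It does not show that a positive result would be spurious.

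The point affects what the trial may conclude, not its sample size or its tests.

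**What to change.** 1. Delete the statement that the results are objective.
2. State as a limitation that participants are unblinded as well as self-selected, and that VAS and the pain and daily-activity parts of CMS are open to expectation bias.
3. Report the range-of-motion and strength components of CMS, scored by the blinded physiotherapist, beside the total CMS as a supportive analysis. If a full protocol or SAP already provides for this, refer to it.
4. Describe any gain confined to self-reported items as patient-reported rather than objective.

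A rule that allows a claim on function only if the examiner-measured part points the same way is not recommended. With no true effect on those components it would be met about half the time, so it would guard poorly against this bias.

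The cost is a change of wording and one added analysis of components of a score already assessed at the planned visits, provided that the component scores are kept. The article does not say whether they are. It describes the study as ongoing, so the analysis can still be specified ahead of the results. The downside is a weaker claim if only the self-reported part moves. Range of motion and strength also depend partly on patient effort, so they are less exposed to expectation but not immune.

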## Data Availability

The datasets used and/or analysed during the current study are available from the corresponding author on reasonable request.

## Abbreviations

PRP: Platelet-rich plasma
CMS: Constant-Murley score
VAS: Visual analog scale
SF-12: The MOS Item Short-form Health Survey
